## Abstract

**Background:**

Living related kidney transplantation (LRT) is underutilized, particularly among African Americans. The effectiveness of informational and financial interventions to enhance informed decision-making among African Americans with end stage renal disease (ESRD) and improve rates of LRT is unknown.

**Methods/design:**

We report the protocol of the Providing Resources to Enhance African American Patients’ Readiness to Make Decisions about Kidney Disease (PREPARED) Study, a two-phase study utilizing qualitative and quantitative research methods to design and test the effectiveness of informational (focused on shared decision-making) and financial interventions to overcome barriers to pursuit of LRT among African American patients and their families. Study Phase I involved the evidence-based development of informational materials as well as a financial intervention to enhance African American patients’ and families’ proficiency in shared decision-making regarding LRT. In Study Phase 2, we are currently conducting a randomized controlled trial in which patients with new-onset ESRD receive 1) usual dialysis care by their nephrologists, 2) the informational intervention (educational video and handbook), or 3) the informational intervention in addition to the option of participating in a live kidney donor financial assistance program. The primary outcome of the randomized controlled trial will include patients’ self-reported rates of consideration of LRT (including family discussions of LRT, patient-physician discussions of LRT, and identification of a LRT donor).

**Discussion:**

Results from the PREPARED study will provide needed evidence on ways to enhance the decision to pursue LRT among African American patients with ESRD.

**Trial registration:**

ClinicalTrials.gov NCT01439516

## Background

African Americans are less likely than Whites to receive kidney transplants, despite their up to four-fold greater likelihood to develop end stage renal disease (ESRD) [1]. Several factors contribute to lower rates of kidney transplantation for African Americans, including immunological incompatibility of deceased donor kidneys [2,3], lower rates of referral of African Americans for transplantation [4-6], lower rates of deceased kidney donation [7], less access to health care [5,8], less desire for kidney transplantation [9,10], and suboptimal discussions about living related kidney transplantation (LRT) between recipients, their families, and health care providers [11]. LRT offers patients an opportunity to bypass many barriers to receipt of deceased kidney transplants, and it improves survival and quality of life at a lesser cost than dialysis care [12-16]. However, African Americans are less likely than Whites to receive LRTs, further exacerbating race disparities in transplant rates [17].

African Americans’ poor awareness of the risks and benefits of LRT as well as their limited access to potential live kidney donors represent important potential barriers to their receipt of LRT [18]. Evidence suggests African Americans are less likely than their White counterparts to be aware of LRT as a treatment option, even when they are under the care of a nephrologist [19,20]. Evidence also suggests African Americans have difficulty identifying potential live kidney donors that successfully complete the donation process [21]. Lack of financial assistance with indirect costs associated with LRT, such as expenses from travel/lodging, lost work, and home health assistance for donors may pose a significant barrier to live kidney donation, particularly among African Americans [22]. A recent study of the general public identified that potential living donors concerned about out of pocket expenses related to donation had 50% lesser odds of being willing to donate when compared to persons not concerned about expenses [23]. In a separate study, an overwhelming majority of the U.S. general public reported having favorable attitudes toward financial assistance programs which could help cover indirect costs for living donors, including costs associated with leave from work, with African Americans reporting significantly more favorable attitudes towards some forms of financial assistance when compared to Whites [24]. To date, however, it is unknown whether educational or financial assistance to address gaps in patients’ knowledge and financial barriers to receipt of LRT could be effective mechanisms of improving African Americans’ access to this life-saving therapy.

We describe the protocol of a two-phase study in which we 1) developed informational and financial interventions to enhance African Americans’ shared and informed decision-making about LRT and 2) are currently testing the effectiveness of these interventions in a randomized controlled trial.

## Methods/design

### Study design summary

The Providing Resources to Enhance African American Patients’ Readiness to Make Decisions about Kidney Disease (PREPARED) Study is a two-phase study to design and test the effectiveness of informational and financial interventions to overcome barriers to pursuit of LRT among African American patients and families. In Phase 1, we developed an informational intervention, including an educational video and handbook, to assist patients with new-onset ESRD and their families with informed decision-making regarding the choice of LRT and other renal replacement therapy options. We also developed a financial assistance intervention for potential live kidney donors identified by patients with ESRD, which we adapted from an existing national program [25]. In Phase 2, we are currently conducting a randomized controlled trial to assess the individual and combined effectiveness of informational and financial interventions on patients’ and their families’ consideration or pursuit of LRT as a treatment. The Johns Hopkins School of Medicine Institutional Review Board has approved all study procedures.

### Phase I: Development of informational and financial assistance interventions

To inform the development of informational interventions, we performed qualitative focus groups as well as directed interviews of patients with kidney disease and their family members. Full details have been previously published [26]. We also performed systematic reviews of scientific evidence describing the risks and benefits of LRT compared to other forms of renal replacement therapy [27-30]. We reviewed the published literature describing ethical and legal forms of potential financial assistance for patients and living donors seeking LRT (e.g. reimbursement for childcare expenses, lodging/travel expenses, and time lost from work) to inform intervention development [31-40]. We also reviewed publicly available information on a national live donor financial assistance program to inform the development of our donor financial assistance intervention [25]. We performed several iterative revisions of informational materials, incorporating feedback from patients with kidney disease and their family members.

### Description of informational intervention

The informational intervention consists of an educational video and written handbook that we designed to assist patients with kidney disease (potential transplant recipients) and their family members (potential donors) with making informed decisions about LRT. The informational materials are intended to expose potential recipients and donors to a variety of experiences of others receiving various forms for renal replacement therapy, including LRT.

The educational video features patients and their family members describing their experiences with LRT as well as with other forms of renal replacement therapy (peritoneal dialysis, home hemodialysis, in-center hemodialysis, and medical management with no dialysis or transplant). The educational video also features medical professionals (a transplant nephrologist, a transplant social worker, a general nephrologist and a dialysis social worker) describing positive and negative experiences patients could have with the various forms of renal replacement therapy. The written handbook provides a summary of scientific evidence describing the risks and benefits of LRT and other forms of renal replacement therapy in lay language. Together, the educational video and handbook promote shared and informed decision-making regarding LRT on the part of patients, their families, and health care providers by achieving commonly accepted goals for informational shared decision-making aids [41].

### Description of the financial assistance intervention

We will offer potential recipients the opportunity to enroll their family members or friends (potential donors) in a program that will reimburse potential donors up to $1600.00 for approved financial assistance through the study by submitting formal original invoices, receipts, and other documentation of their qualifying medical and non-medical expenses related to live kidney donation evaluation, donation, or convalescence (up to 10 weeks post live donor/LRT procedures). Qualifying expenses include travel/lodging, meals, incidental expenses (e.g., parking), lost wages, and childcare costs incurred by the potential donor as part of: (1) donor evaluation, clinic visit or hospitalization, (2) hospitalization for the living donor surgical procedure, and/or (3) medical or surgical follow-up clinic visits or hospitalization within 90 days following the living donation procedure. Participants will be permitted to utilize the $1600.00 for multiple approved purposes, as long as the total reimbursement is not greater than $1600.00. Also, more than one potential donor may draw from these funds, as long as the total value of reimbursed expenses does not exceed $1600.00 per patient study participant. This program covers a broader array of expenses related to live kidney donation than other national programs and does not limit reimbursement of potential donors based on their personal incomes.

### Phase 2: Randomized controlled trial assessing the individual and combined effectiveness of informational and financial interventions

We are currently conducting a randomized controlled trial to assess the individual and combined effectiveness of informational and financial assistance interventions to enhance rates of LRT. The combined intervention will be tested to detect any additive or multiplicative effects of the financial assistance intervention. Recruitment of study participants began in August, 2012. Figure 1 contains a flow diagram demonstrating the overall structure of our study.

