#### Randomization

Using blind and secure allocation by computer, we randomly assign participants to one of three intervention arms: 1) control group (“Usual Care”, N=70); 2) the informational intervention (“PREPARED”, N=70); and 3) the informational plus the financial assistance interventions (“PREPARED plus Financial Assistance”, N=70). Randomization is blocked by recruitment site to ensure equal allocation within each dialysis facility.

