#### Sample size and power

We are aware of no other randomized controlled trials evaluating the effectiveness of informational (focused on shared decision-making) or financial interventions on commitment to LRT in incident dialysis patients. In our own work, an educational intervention resulted in patients’ greater pursuit of LRT (30% achieving new LRT behavior in Usual Care arm compared to 50% in education arm over 6 months) [19]. Our own previous work also demonstrated African Americans in the US general public were supportive of live kidney donors receiving reimbursement for expenses related to donation [24]. We anticipate the financial intervention, which addresses a common and tangible barrier to live kidney donation, may improve pursuit of LRT by an additional 10%. Based on these assumptions, we will have over 80% power to detect a trend of increasing pursuit of LRT across groups (e.g., 30% in Usual Care, 50% in PREPARED group, 60% in PREPARED plus Financial Assistance group) at 6 months. We will also have over 80% power to detect a 30% difference between the PREPARED group and the Usual Care group or the PREPARED plus Financial Assistance group and the Usual Care group individually with correction for multiple comparisons.

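### The three arms cannot give a stand-alone or interaction effect of financial assistance, and the one financial effect they can give, the increment over PREPARED, is not powered

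*Protocol article*

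**What the plan says.** The Study design summary describes a randomised trial "to assess the individual and combined effectiveness of informational and financial interventions". The opening of the Phase 2 section repeats this aim and adds: "The combined intervention will be tested to detect any additive or multiplicative effects of the financial assistance intervention".

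Under Randomization, "we randomly assign participants to one of three intervention arms": Usual Care, PREPARED (video and handbook), and PREPARED plus Financial Assistance, with 70 participants each. No arm receives financial assistance without the informational materials.

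Sample size and power assumes 6-month rates of 30%, 50% and 60%, so the money is expected to add 10 points to PREPARED. It states "we will have over 80% power to detect a trend of increasing pursuit of LRT across groups", and also more than 80% power for a 30-point difference between either active arm and Usual Care after multiplicity correction. It gives no power for the combined arm against PREPARED.

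Data analysis takes assigned group as the main explanatory variable, compares group proportions, and plans multivariable models such as logistic regression. It lists no specific contrasts and no trend test.

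**The concern.** Financial assistance is one of the two interventions under test, and the Discussion looks ahead to evidence that could support wide adoption. The stated aim promises effects that these arms do not contain. The financial effect that they do contain is absent from the power statement.

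Two misreadings become possible. A significant trend, or a significant result for the combined arm against Usual Care, could be credited to the money when the video and handbook produced all of it. Conversely, a non-significant combined-versus-PREPARED result could be taken to show that money does not help, when the trial had little chance of detecting the assumed benefit.

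**Working it through.** **Inputs.** From Randomization: 70 per arm. From Sample size and power: rates p1 = 0.30 (Usual Care), p2 = 0.50 (PREPARED), p3 = 0.60 (combined). The article states no alpha, sidedness, trend-test form or dropout rate. I assume two-sided 0.05, a Cochran-Armitage test with scores 0/1/2, and no dropout, and show ranges.

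**Identification.** Let m be the unobserved rate with money alone.
- Stand-alone effect: m − p1.
- Additive interaction: p3 − p2 − m + p1.
- Multiplicative interaction: p3·p1 / (p2·m).

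Each contains m, which no arm supplies. The planned 30/50/60 fits all of these illustrative values:
- m = 0.40: additive interaction 0.60 − 0.50 − 0.40 + 0.30 = 0.
- m = 0.36: multiplicative ratio 0.60 × 0.30 / (0.50 × 0.36) = 1.
- m = 0.30: no stand-alone effect; additive interaction 0.60 − 0.50 − 0.30 + 0.30 = 0.10.

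The data cannot choose among them. Only p3 − p2, the increment given the information, is identified.

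**The plan's own figures.** With equal arms and equal spacing, the trend numerator is p3 − p1. PREPARED enters only through the pooled rate p̄ in the null variance.

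Power ≈ Φ{[(p3 − p1) − 1.96·√(2p̄(1 − p̄)/n)] / √[(p1(1 − p1) + p3(1 − p3))/n]}

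- 30/50/60: p̄ = 0.467; null SE 0.0843; alternative SE 0.0802; (0.300 − 0.165)/0.0802 = 1.68; power 95% (simulation 95.3%). With 56 per arm (20% dropout): 90%.
- 30% v 60% pairwise: 95% at 0.05, 92% at 0.025, 89% at 0.0167.

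Both claims of more than 80% hold.

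**Does the trend isolate the money?**
- 30/50/50 (money adds nothing): p̄ = 0.433; null SE 0.0838; alternative SE 0.0811; (0.200 − 0.164)/0.0811 = 0.44; significant 67% of the time (simulation 67.2%). With 56 per arm: 57%.
- 30/50/45 (combined arm worse than PREPARED): 43%.
- 30/50/40: 22%.

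**The direct contrast, 50% v 60%.** p̄ = 0.55; null SE √(2 × 0.55 × 0.45/70) = 0.0841; alternative SE √((0.25 + 0.24)/70) = 0.0837.

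| Alpha | Power | n per arm for 80% |
|---|---|---|
| 0.05 two-sided | 21.9% | 388 |
| 0.025 (two comparisons) | 14.5% | 470 |
| 0.0167 (three comparisons) | 11.3% | 517 |

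A one-sided 0.05 test would reach 32%. The 95% CI half-width is 1.96 × 0.0837 = 0.164. With 70 per arm, 80% power at two-sided 0.05 needs a difference of about 23 points from 50%.

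**The case against.** Several stronger readings are tempting, and the article does not support them.

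- A reader might infer that no combined-versus-PREPARED comparison is planned. That is not shown. The three-group model can yield it, no pairwise contrast of any kind is listed in Data analysis, and a contrast list may sit in an analysis plan that is not shown. What can be said is that this contrast is neither named nor powered here.
- A reader might infer that the trial's conclusion rests on a trend test. The trend appears only in the power paragraph, beside two pairwise comparisons. The stated primary analysis is group proportions and multivariable models.
- A reader might infer that the sponsor will credit a significant trend to the money. No section says so. The 67% measures a risk of misreading and is not the error rate of a stated rule.

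It can also be argued that additive or multiplicative is loose language for whether the money adds to or amplifies the information effect, which suits an add-on design. On that reading the combined-versus-PREPARED contrast does estimate the increment. But adding still cannot be told from amplifying without a money-only rate, and the promise of an individual financial effect remains unmet. No analysis plan can repair that.

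Finally, the low power contradicts no stated figure, because none is claimed for this contrast. That is correct. The gap is between the question promised and the questions powered.

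**Conclusion.** The aim is wrong as written. With these arms, neither a stand-alone financial effect nor an additive-versus-multiplicative interaction can be estimated. This follows from the allocation alone and needs no numerical assumption. The individual effect of the informational intervention, PREPARED v Usual Care, is unaffected.

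The one identifiable financial effect has about 22% power at the protocol's own 10-point increment, or 11% to 15% with multiplicity correction, and would be estimated to within about ±16 points. The powered comparisons do not stand in for it: the trend is significant about 67% of the time when the money adds nothing, and the combined arm against Usual Care mixes both components. These figures rest on the assumed two-sided 0.05, scores 0/1/2, 70 per arm and no dropout. Dropout would lower the power further. The stated power figures need no change.

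**What to change.** 1. In the Study design summary and the opening of the Phase 2 section, replace the individual-and-combined and additive-or-multiplicative wording with three estimable effects: PREPARED v Usual Care; the combined package v Usual Care; and Financial Assistance added to PREPARED.
2. Name combined v PREPARED as the comparison that answers the financial question. Report it as a risk difference with 95% CI, obtained from the existing model's predicted probabilities.
3. In Sample size and power, keep the present figures and add that the trial is not powered for the assumed 10-point increment (about 22% at two-sided 0.05), so a non-significant result there is inconclusive.
4. State that any claim about financial assistance will rest on that contrast, and not on the trend or on the package v Usual Care result.

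No new arm or participants are needed. The cost is some wording, one contrast from the same model, a narrower aim, and a less favourable stated power for the financial question.

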**Figure 1 F1:**
[figure not shown]
Flow of PREPARED Study Activities.

#### Target population and eligibility criteria

Our population includes English-speaking African American patients with ESRD who are age 18 years or older and who have initiated dialysis within one year prior to study enrollment. We exclude participants if they have dementia (assessed in-person) [42] or if they have a self reported history of prior kidney transplant, cancer within 2 years prior to recruitment, stage IV congestive heart failure, end stage liver disease, pulmonary hypertension, severe peripheral vascular disease, or chronic (debilitating) infections. We assess participants’ eligibility via questions administered by a research assistant in-person in dialysis units. After potentially eligible patients agree to participate, we request a release of medical records from each participant to confirm their eligibility for the study and to ascertain whether potential donors have contacted local transplant centers to be evaluated as donors on behalf of participants.

#### Recruitment of participants

We recruit participants from academically affiliated and community-based dialysis centers in the Baltimore, MD metropolitan region, which we have selected to provide an adequate number of African American participants with new-onset ESRD. We recruit patients on-site from different dialysis centers on different days. We systematically rotate recruitment days at sites so variations in patient scheduling at all sites can be covered to achieve the maximum number of recruitment opportunities. Upon confirmation of their eligibility to participate, we randomly assign patients into intervention groups.

#### Reimbursement and enrollment of potential kidney donors

Potential kidney donors only become aware of the financial assistance program through direct referral by enrolled study participants. Research study staff do not contact or attempt to contact any family, friends, or acquaintances of enrolled patient participants. Therefore, enrolled participants will be directed to contact study staff in the event they want to refer potential donors to the program. To be eligible to participate, potential donors must speak English and be 18 years or older. Once potential donors contact study staff, study staff arrange for a time to meet with the potential donor(s) in person and mail them the brochure describing the financial assistance program. At that time, study staff explain the financial assistance program to potential donors, including what they will be asked to do as part of the study. Potential donors are notified that participation in the financial assistance program offered by the study may preclude them from receiving financial assistance from any other program (e.g., National Living Donor Assistance Center). If potential donors wish to participate in the financial assistance program, we obtain consent for their participation in the study using approved consent procedures.

#### Randomization

Using blind and secure allocation by computer, we randomly assign participants to one of three intervention arms: 1) control group (“Usual Care”, N=70); 2) the informational intervention (“PREPARED”, N=70); and 3) the informational plus the financial assistance interventions (“PREPARED plus Financial Assistance”, N=70). Randomization is blocked by recruitment site to ensure equal allocation within each dialysis facility.

#### Usual care group

Participants randomly assigned to receive Usual Care proceed with their clinical care in dialysis centers as already routinely implemented by their physicians. At study conclusion, participants will receive informational materials provided in PREPARED (educational video and written handbook) after follow up assessments have been completed.

